### Trial design

The design is a pragmatic, cluster randomised controlled parallel group trial with one intervention arm (Let’s Move It programme) compared with control arm (standard curriculum). The trial is a superiority trial. The first and second batches of the trial serve as an internal pilot study. The internal pilot data was subject to interim analysis in line with the analysis plan to investigate previous assumptions and to make adjustments to the data collection plan.

Control and intervention arms include altogether 57 classes (intervention *k* = 30, control *k* = 27). The school is the unit of cluster randomisation, but classes are the units of cluster analysis. A cluster randomisation based on school was chosen for practical reasons and to prevent contamination. The level of class (student group) will be the cluster unit of analysis, as the essential part of the intervention is delivered in the group setting, and the nestedness of individuals in the classes may influence the individual outcomes due to e. g. group dynamics and emerging norms. Matching schools by type of educational tracks they offer (e.g. business, nursing) [21] results in the same educational tracks being allocated to both intervention and controls. Paired units were randomly assigned to intervention or control. The intervention is provided as normal part of the school. The details of the trial have been planned to avoid the typical sources of bias in health behaviour RCTs [22], including using a strict protocol for participant contact (performance bias), cluster randomization (contamination bias), and objective outcome measurement.

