### Participants and eligibility criteria

Participants are vocational students in study year 1 and 2 (typically aged 15–17). All students will be invited to take part. Of educational tracks, those that meet the following criteria were selected for the study: Those educational tracks whose 1) students, compared to other educational tracks in the Finnish National School Survey, report on average higher levels of SBs and 2) report lower levels of PA on their leisure-time, 3) student intake in the national system is high to meet sample size requirements, and 4) future occupations that are either sedentary or require adequate/good physical condition. These educational tracks were selected based on evidence (Finnish National School Health Promotion survey, THL) and active consultation with the study scientific steering committee and with stakeholder expert group meetings, and the educational tracks were ranked as follows: 1. Business and administration, 2. Business information technology, 3. Nursing, 4. Hotel, restaurant and catering studies, 5. Tourism, 6. Car mechanics. The final selected combination of tracks (1.-4.) allowed for an even proportion of boys and girls in the trial. Next, the eligibility criteria are explained for schools, classes, individual students, and individual teachers.

(1) **Vocational schools**. Of the vocational schools within the study region, we decided to select schools that have the highest number of starting students in selected educational tracks (to meet sample size requirements). Six school units were recruited. In these schools, the trial aims to include the maximum number of classes in years 1 and 2 in the selected educational track present in the school during the study period (and not in vocational work practice outside school).

Schools had to agree to randomisation, allow teachers to participate in the Let’s Move It workshop training, scheduling the Let’s Move It student program in their curriculum and be representative of Finnish vocational schools.

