### Recruitment

Recruitment of schools, classes and students occurs through several phases.

(1) Six vocational schools or school units were recruited in autumn 2014. The schools in the Helsinki Metropolitan area that cater for the selected educational tracks were ranked in the order of size of intake of students in that educational track. The suitability according to selection criteria determined the order in which the eligible upper secondary schools were approached to participate. Once randomised, schools either deliver Let’s Move It as part of their curriculum (intervention) or continue to offer PE and health education as part of their usual curriculum (control).

A letter was sent to directors of the selected schools (summer/autumn 2014), informing about the study and inviting participation, including a letter of support from the Finnish Board of Education recommending participation in the Let’s Move It trial. Then, the principal was contacted by phone by a member of the research team, following by a face-to-face meeting to outline the requirements of the study. Invitations to participate were sent to schools, and if a selected school declined, a letter was sent to the next eligible school on the list that matches the matched-pair school according to the criteria. School principals gave consent prior to randomization and thus were blind to randomisation. Out of all school units (8) contacted, two schools did not accept the request for the research team to present the project more in detail, due to heavy workload or other similar interventions going on already at the school. Six schools consented.

(2) Following randomisation of schools, eligible classes of first and second year students were enrolled, typically with final confirmation a few weeks before the baseline measurement. The trial was commenced in January 2015, and data are collected in six batches, with the same educational tracks measured in parallel in both intervention and control arms: business/IT (Batches 1 and 2, spring 2015), nursing (Batches 3 and 4, autumn 2015), and hotel, restaurant and catering (Batches 5 and 6, spring 2016, ongoing) (Fig. 3).

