#### Primary outcome measures

Objectively measured outcomes (MVPA, sedentary time, breaks in sedentary time) are based on accelerometry [32]. The 3-axial accelerometer (Hookie AM 20, Traxmeet Ltd, Espoo, Finland) has been shown to be a valid measurement tool both among adults [32] and young people [34]. The accelerometer is fixed to an elastic belt and participants are instructed to wear the belt on their hip for seven consecutive days during waking hours, except during shower and other water activities, starting from the delivery day. The accelerometers collected and stored the tri-axial data in raw mode in actual acceleration (g-units). The data is analysed in 6 seconds’ epoch length. PA was categorised into three intensity categories based on metabolic equivalents (MET): light, moderate and vigorous. Light PA is defined as activity corresponding 1.5−2.9 MET, moderate activity as 3.0–5.9 MET and vigorous activity more than 6 MET [35]. According to the definition of SB [36], time spent in sitting and reclining positions are combined to indicate SB, time standing still is analysed separately. It is possible to accurately determine whether the participant is standing, sitting or lying by applying the information from the raw data of the three measurement axes of the accelerometer. While the body position during walking is upright and the direction of Earth’s gravity vector is constant, the vertical position (angle) of the accelerometer can be identified during normal walking. This known position can then be used to recognise different body postures. In standardised conditions, standing can be separated from sitting or lying with 100 % accuracy [37]. Breaks in sedentary time are calculated on the basis of the number of lying/sitting periods ending-up with a clear vertical acceleration.

Research assistants deliver the accelerometers to the participants in schools, and they collect them the subsequent week at the school. All participants are instructed not to change their usual or intended patterns of activity when wearing the accelerometer. Self-reported PA during leisure time will be assessed using the validated NordPAQ measure [38] in the questionnaire, concerning MVPA over the previous seven days. The assessments take place concurrently in both intervention and control arms to control for the effect of weather conditions on activity. The assessors are not involved in intervening on students.

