### Statistical analyses

Effectiveness analyses will be conducted according to the intention-to-treat principle. Primary and secondary outcomes will be analysed using generalised linear mixed model (GLMM) that will allow to take into account correlations between observations. These methods also allow the incorporation of incomplete longitudinal data into the analysis. Additional sensitivity analysis using the “as treated” approach will be conducted in order to gauge efficacy. Process analyses will include e.g. multiple mediation models to test whether the impact of the intervention is explained by its effect on the hypothesised mediators. We will conduct the outcome analyses separately for gender and different levels of baseline activity. When allowed by time and funding resources, we will also conduct the analyses by educational track, parental SES, and baseline body composition. Quantitative analyses will be conducted using the R, SPSS and the Mplus statistical softwares.

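### Differences in effect between track groups coincide with calendar period and rest on few schools, and separate fits for boys and girls do not test a gender difference

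*Protocol article*

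**What the plan says.** Statistical analyses states the subgroup plan in two sentences. The gender part is unconditional: "We will conduct the outcome analyses separately for gender and different levels of baseline activity". The by-track part depends on time and funding: "we will also conduct the analyses by educational track, parental SES, and baseline body composition". Neither carries a caveat about how track is tied to other features of the design.

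Recruitment gives the calendar: "business/IT (Batches 1 and 2, spring 2015), nursing (Batches 3 and 4, autumn 2015), and hotel, restaurant and catering (Batches 5 and 6, spring 2016," the last of these still under way at the time of writing. It adds that data are collected "with the same educational tracks measured in parallel in both intervention and control arms". Primary outcome measures gives the reason: "The assessments take place concurrently in both intervention and control arms to control for the effect of weather conditions on activity".

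Trial design describes "Matching schools by type of educational tracks they offer", with the paired units then randomised and the class taken as the unit of cluster analysis. Randomisation procedure and blinding adds school size as a matching factor. The abstract gives six schools, three per arm.

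On gender, Participants and eligibility criteria says that the chosen combination of tracks "allowed for an even proportion of boys and girls in the trial". The gender share within each track is not given.

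**The concern.** A by-track analysis invites the reading that the programme works in one occupation and not in another. In this design each track group has its own enrolment period, so such a pattern could equally reflect the time of year, the calendar year or a change in delivery over time. With only six schools it could also reflect ordinary differences between a few schools.

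Gender raises a related but weaker issue. If boys and girls are spread unevenly over tracks, two separate fits average over different mixes of tracks, periods and schools. Setting the two results side by side then mixes gender with track. The comparison is an obvious one to make: the Background section reports that earlier school interventions changed activity mainly in girls, and Aims of the study states the hypothesis for both genders.

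What is at stake is the interpretation of subgroup results, not the main contrast between arms.

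**Working it through.** **Inputs from the protocol article.** Target effect d = 0.30, 176 per arm (352 in total), objective MVPA ICC 0.059, class size 17 (SD 3.83), stated design effect 2.00, 703 students needed (Sample size); 1100 × 0.8 × 0.8 = 704 after dropout.

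**Reproducing the plan's figures.** The two-sample formula at d = 0.30, two-sided 5% and 80% power gives 175 per arm (normal approximation) or 176 (t-test). With CV = 3.83/17, the design effect is 1 + ((CV² + 1) × 17 − 1) × 0.059 = 1.995, and 352 × 1.995 = 702. These match the stated 176, 2.00 and 703. No figure is stated for any track or gender analysis.

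**Which effects can be separated.**
- *Track group and period.* Each of the three track groups occupies one period, so the arm × track-group and arm × period terms are the same columns under any school layout. No model separates them. Business/IT and catering both run in spring, so that one contrast is free of time of year but not of calendar year. Business and IT share a period and can be compared with each other free of it.
- *Track group and school pair.* If each track group sits in one pair (assumption), a model with pair and pair × arm has rank 6, and adding arm × track leaves it at 6: complete aliasing. If each track group spans two pairs (equally an assumption), the rank rises from 8 to 10 and the two can be separated.
- *Gender.* Even with one pair per track group, adding gender and arm × gender raises the rank from 6 to 7 to 8. Gender effect modification is estimable within track and pair, unless tracks are single-sex, which is not stated.

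**Precision of a by-track estimate.** Assume three equal track groups and class clustering only. Then 704/3 = 234.7 students, or 117.3 per arm; 117.3/1.995 = 58.8 effective per arm; SE = √(2/58.8) = 0.184. Power for d = 0.30 is about 37%, and the effect detectable with 80% power is about 0.52. A difference between two track groups has SE 0.184 × √2 = 0.261, a 95% half-width of about 0.51 SD, which exceeds the target effect.

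**School differences within a track.** Assume that between-school variance is 1% or 2% of the total (not in the document), with k pairs per track group. With the stated design effect the nominal SE is √(4 × 2.0/234.7) = 0.185. The true variance adds 2 × ICC_school / k, and the type I error is 2 × (1 − Φ(1.96 × 0.185/SE_true)).

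| Pairs per track group | 1% school variance | 2% school variance |
|---|---|---|
| 1 | 12.0% | 18.4% |
| 2 | 8.5% | 12.0% |
| 3 | 7.3% | 9.7% |

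If the school variance is already part of the 0.059, the first row becomes 11.0% and 16.6%.

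**Track mix carried into gender fits.** Assume equal track sizes, track effects of 0.2/0.4/0.3 SD and no gender difference within any track. With girls' shares of 20/90/60%:
- girls: (0.20 × 0.2 + 0.90 × 0.4 + 0.60 × 0.3)/1.70 = 0.58/1.70 = 0.341
- boys: (0.80 × 0.2 + 0.10 × 0.4 + 0.40 × 0.3)/1.30 = 0.32/1.30 = 0.246
- gap: 0.095

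At 40/70/60% the gap is 0.54/1.70 − 0.36/1.30 = 0.041. With equal shares across tracks it is 0. All these inputs are assumed. The two unequal sets average 1.70/3 = 57% girls, so they do not exactly match the even split that the article reports.

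**The case against.** The strongest reply has four parts.

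1. Both arms of a track are measured at the same time, so season cannot bias the effect estimated within a track. This stands. A reader might infer from the calendar that by-track effects are distorted by season; the documents do not support that. Only comparisons between track groups are tied to period.
2. A reader might also infer that every track is one school against one school. The article does not say so: it speaks of the tracks, in the plural, that schools offer, and gives no layout. This stands too, and it makes the school part of the point conditional.
3. It is tempting to say that gender effects cannot be separated from track, period and school. That is wrong, because gender varies between students within tracks. Moreover, the stated hypothesis compares arms within each gender, not boys with girls. Separate fits give valid average effects for the boys and girls enrolled; only attributing a gap between them to gender would be unsafe. What remains is that two fits provide no test of a difference and that side-by-side reading carries over track mix.
4. The by-track analysis is optional, and interaction terms and subgroup labels commonly belong in an SAP, which is not shown. Their absence is therefore no fault in itself. The point rests on what the article does state: separate fits by gender, and by-track analyses in a design where track group and period coincide.

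The type I figures rest on assumed school variance and arise from modelling classes when schools were randomised. That is a separate matter and should not be charged to the subgroup plan alone.

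**Conclusion.** The point holds in a limited form. A difference in intervention effect between the three track groups is fully confounded with calendar period. It may also be confounded with differences between a few schools, depending on a layout that is not given. By-track estimates would be imprecise as well: about 37% power for d = 0.30, assuming three equal groups. Under assumed school variance of 1–2%, a nominal 5% within-track test would have a type I error of roughly 7–18% across one to three pairs per track.

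Gender effect modification is estimable. The planned separate fits do not test it, and comparing them would carry over any difference in track mix: 0.00 to about 0.10 SD under assumed track effects and gender shares, not computable from the document itself.

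The primary analysis is not affected by this point. The consequence lies in what may be concluded from subgroups.

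**What to change.** In Statistical analyses:

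(a) State that by-track results are descriptive estimates with intervals, labelled as track-period-school results, and that differences between them will not be attributed to track.

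(b) Replace the separate gender fits by one model with arm × gender, adjusted for track (batch) and arm × track. Report the gender-specific effects and their difference from that model, so that boys and girls are compared within the same track and period.

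The cost is a few sentences and some extra model terms; no new data are needed. The downside is wider intervals for the subgroup contrasts, especially if some tracks contain few boys or few girls.

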## Discussion

The study will address central gaps in the evidence base. The RCT will test the effectiveness of a multi-level theory-based intervention to increase activity among adolescents. To date, only three RCTs in this domain have evaluated effects on PA over the long-term, beyond one-month post-intervention [9]. This trial will show whether adding a carefully designed, evidence- and theory-based program will add value to teaching as usual. The analysis of intervention and BCT uptake and target groups’ experiences provide both theoretically interesting insights and also practically useful ideas to optimise intervention activities before wider dissemination. Investigations of fidelity and its predictors will provide practical help in the later dissemination phase in targeting key determinants and activities critical for maintenance.

To our knowledge, this is the first school-based PA intervention specifically targeted at vocational schools and tested in a randomised trial. The intervention addresses both individual and environmental features and provide evidence regarding the causal mechanisms and implementation, and their relation to outcomes. This matched pair design improves comparability of the arms (balanced for the most important covariates, gender and educational tracks) and thus improves power. Contrary to prior RCTs in the area that used an individual-level design, our class-level cluster design acknowledges the potential effect of small group dynamics on receipt of intervention activities delivered at class level.

The phased approach in development, combined with participatory process with end-users, may minimise risks such as infeasibility with the setting and target group, failure in recruitment, and inefficacy in producing or detecting the desired changes in behaviour due to inappropriate BCTs or poor statistical power. After the project ends, the anonymised dataset will be made available to other researchers.

The project also produces a practical program to be utilised in the Finnish school context. In line with the MRC recommendation [40, 41], we aim to promote dissemination and translation of the program into routine practice after completion of the trial. Vocational school students would benefit from increases in PA in terms of improved work capacity and mental well-being [4]. Intervention protocols including comprehensive manuals will be made available in the public domain, as well as the student workbook and other materials. The program components have the potential to be translated to be a part of the standard curriculum: Vocational school teachers, following appropriate training, can teach the student programme, the dose is easily embeddable in the school practices, and the student group program is compatible with the national curriculum learning objectives for health education. Thus, this intervention has high potential for dissemination. In order for a successful implementation into practice, the adoption should be supported by a training programme, consisting of a train-the-trainers manual, pre-intervention training, supervision and auditing organised by the research group, peer support and feedback systems at the schools, and on-line facilitator support materials.

### Ethical board

The Hospital District of Helsinki and Uusimaa, The Ethics Committee for gynaecology and obstetrics, pediatrics and psychiatry (decision number 367/13/03/03/2014.

### Trial status

Recruitment started in January 2015 and is ongoing.

## Abbreviations

BCT: behaviour change technique
BMI: body mass index
MVPA: moderate-to-vigorous physical activity
PA: physical activity
SB: sedentary behaviour
SES: socioeconomic status
